**Fig. 1 Fig1:**
[figure not shown]
Natural progression of hepatitis C virus (HCV) infection (**A**) and the HCV care continuum (**B**). SVR, sustained virologic response 12 weeks of completion of treatment

The overall objectives of the *D*etermining *E*ffective *T*esting in *E*mergency Departments and *C*are Coordination on *T*reatment Outcomes (DETECT) for *Hep*atitis *C* (Hep C) study are to (1) compare the effectiveness of two forms of HCV screening—non-risk-based (nontargeted) and risk-based (targeted) HCV screening (Screening Trial)— [20] (2) compare the effectiveness of two forms of referral to treatment for ED patients identified with HCV—linkage navigation plus clinician referral versus clinician referral alone (Linkage-to-Care Trial), (3) measure and compare programmatic costs and project long-term clinical outcomes, costs, and cost effectiveness of ED-based HCV screening and linkage-to-care (Cost Evaluation), and (4) examine the effects of disparities and social determinants of health on linkage-to-care, treatment initiation, and treatment completion among patients identified with HCV in the ED (Disparities and Social Determinants of Health Evaluation).

This article describes the rationale and design for the Linkage-to-Care Trial and is reported in accordance with the SPIRIT Statement for clinical trials [21, 22]. The primary hypothesis for the Linkage-to-Care Trial is that linkage navigation in addition to clinician referral will significantly increase the proportion of newly HCV-diagnosed individuals who complete care visits and initiate treatment when compared to clinician referral alone. The protocol (Version 3.3, Date February 17, 2022) is provided in the Additional.

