### Data collection

During this trial, an assessment of barriers and facilitators to linkage to HCV care will be conducted through use of an audio computer administered self-interview (ACASI) offered to all enrolled patients after informed consent has been obtained but before randomization. ACASI has been shown to be a superior method for collecting potentially sensitive information in an efficient and anonymous format [25]. The survey will be offered in English and Spanish and will collect the following data for all enrolled patients: (1) ED visit information (unique study identifier, date/time of the visit), (2) demographics (age, gender, race, ethnicity, primary language), (3) payer information (commercial, Medicare, Medicaid, self), (4) detailed contact information, (5) details of randomization, (6) clinician referral information, (7) HCV RNA testing, (8) linkage navigation details, and (9) all outcome measures. Data from (1) through (6) will be collected prospectively by a trained research assistant during enrollment, data from (7) will be collected retrospectively by a trained research assistant, data from (8) will be collected prospectively by the linkage navigator, and data from (9) will be collected by a trained research assistant, blinded to intervention allocation and distinct from the research assistant who will perform enrollment. All retrospective data collection will use structured methods. In prior HIV studies, we have consistently obtained longitudinal follow-up for > 90% of HIV-diagnosed patients from the ED thus we anticipate collecting similarly high HCV follow-up data [26, 27].

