### Statistical methods

Analyses will be performed using the intention-to-treat principle. Bivariate statistical tests will be used to compare variables, including results from the ACASI surveys between study groups. Given the randomized design, the primary comparison will include the absolute percentage difference and risk ratio with 95% CIs for initiation of HCV treatment (primary outcome) and will be tested using chi-square or Fisher’s exact test. Kaplan-Meier and Cox proportional hazard regression will be used to estimate associations between the interventions and outcomes when modeled using time-to-event as an outcome. One interim effectiveness analysis is planned and will be performed by the study’s biostatistician while maintaining blinding to study arm allocation. Using the approach by O’Brien-Fleming, the interim analysis will occur at the study’s halfway point, after 140 total patients (approximately 35 per arm) have been enrolled and outcomes data collected, and with an effectiveness threshold of *p* < 0.0054 for the primary outcome. A non-binding futility threshold of *p* > 0.5 will be used for the primary outcome. If the trial is not stopped after the interim analysis, it will proceed to enroll the full sample (280) with a significance effectiveness threshold of *p* < 0.0492. The unit of analysis will be the patient. Secondary analyses will include comparisons of all other outcomes by study arm with subgroup analyses for the stratum of individuals < 40 years of age or PWID, age, gender, race, ethnicity, income, and education level.

Additional secondary analyses were planned a priori to evaluate disparities and the effects of social determinants of health (SDoH) on linkage, treatment initiation, and SVR12. Multivariable logistic regression analyses will be used to estimate the associations between gender and study outcomes while adjusting for confounders, including but not necessarily limited to age, race, ethnicity, housing status, HCV knowledge, and willingness to engage in care. Additionally, effect modifiers (e.g., race, ethnicity and gender, age and gender) will be evaluated. The statistical approach will be variable centered and will use hierarchical multivariable logistic regression to estimate associations between SDoH characteristics and linkage to care, treatment initiation, and SVR12. We will use a theoretical framework and prior studies to inform covariate selection to assess the relationships between SDoH and the outcomes.

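### The gender model adjusts for housing, HCV knowledge and willingness to engage in care as confounders, though these may be mediators, so the estimate can understate the disparity it is meant to measure

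*Protocol article*

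**What the plan says.** The Introduction of the protocol article lists, as its fourth overall objective, to "examine the effects of disparities and social determinants of health on linkage-to-care, treatment initiation, and treatment completion". The second paragraph of Statistical methods carries this out. It states that "Multivariable logistic regression analyses will be used to estimate the associations between gender and study outcomes" and describes the model as "adjusting for confounders, including but not necessarily limited to age, race, ethnicity, housing status, HCV knowledge, and willingness to engage in care". The list mixes three demographic variables (age, race, ethnicity) with three of another kind (housing, knowledge, willingness) and gives all six the same role.

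The same paragraph plans a separate set of models for social determinants, which "will use hierarchical multivariable logistic regression to estimate associations between SDoH characteristics and linkage to care, treatment initiation, and SVR12".

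**The concern.** A variable that is a consequence of the exposure and also affects the outcome is a mediator. Adjusting for it changes the question from how much outcomes differ by gender to how much they differ among people with the same value of the mediator. Housing, HCV knowledge and willingness could each differ by gender and affect whether a patient reaches care. Willingness is the clearest case because it lies close to the outcomes themselves, linkage and treatment initiation.

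A gender gap in treatment that arises through unstable housing or lower willingness is still a disparity. A model that holds those variables fixed can report a smaller gap than exists. Calling the variables confounders suggests that the adjusted figure is the cleaner estimate of the same quantity, when it estimates a different one.

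Age, race and ethnicity do not raise this problem. They are not consequences of gender, so adjusting for them is ordinary demographic standardisation.

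**Working it through.** The documents give no figure for the gender analysis, so there is nothing to reproduce. The check has two parts: whether any other text supplies the total gender association, and how far adjustment for a mediator could move the estimate.

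**Part 1: the text.**
- The hierarchical regression is stated for social determinants. No contrast of the gender coefficient before and after adding a block of variables is described.
- Theory-based choice of covariates is also tied to the social-determinant models: "We will use a theoretical framework and prior studies to inform covariate selection to assess the relationships between SDoH and the outcomes". For gender, covariates are already named.
- The unadjusted comparisons are between trial arms: "Bivariate statistical tests will be used to compare variables, including results from the ACASI surveys between study groups".
- The planned gender subgroup analysis compares outcomes by study arm within gender. It does not compare the genders.
- The survey is described under Data collection: "an assessment of barriers and facilitators to linkage to HCV care will be conducted". This treats such variables as steps that help or hinder reaching care, which concerns their relation to the outcome. It says nothing about their relation to gender.

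No sentence states a total or demographics-only gender association, or says that a conditional association is the target.

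**Part 2: size. All inputs are assumptions; none comes from the documents.**

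*Complete mediation, simple case.* Assume initiation is 30% if willing and 10% if not, and that gender has no other effect.
- Willingness 70% vs 50%: 0.7×0.3 + 0.3×0.1 = 0.24 and 0.5×0.3 + 0.5×0.1 = 0.20. The total OR is (0.24/0.76)/(0.20/0.80) = 1.26.
- Willingness 80% vs 40%: 0.8×0.3 + 0.2×0.1 = 0.26 and 0.4×0.3 + 0.6×0.1 = 0.18. The total OR is (0.26/0.74)/(0.18/0.82) = 1.60.

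The willingness-adjusted OR is 1.00 in both, but only because complete mediation was assumed.

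*Partial and no mediation.* Let g be gender (0 or 1), π_g the mediator prevalence (centred at 50%), OR_M the mediator–outcome odds ratio and OR_D the direct gender odds ratio. Then

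p_g = π_g · expit(b + ln OR_M + g·ln OR_D) + (1 − π_g) · expit(b + g·ln OR_D),

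with b set so that the average of p_0 and p_1 is 20%. The total OR is [p_1/(1−p_1)]/[p_0/(1−p_0)], the adjusted OR is OR_D, and the share removed is 1 − ln(OR_D)/ln(total OR).

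Worked line: with a gap of 20 points, OR_M = 4 and OR_D = 1.5, p_0 = 0.150 and p_1 = 0.250. The total OR is (0.250/0.750)/(0.150/0.850) = 1.89, and the share removed is 1 − 0.405/0.637 = 0.36.

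| Gender gap in mediator | OR_M | Total OR if OR_D = 1.0 | Total OR if OR_D = 1.5 | Share of log OR removed if OR_D = 1.5 |
|---|---|---|---|---|
| 0 points | 2 | 1.00 | 1.49 | −2% |
| 0 points | 4 | 1.00 | 1.46 | −7% |
| 10 points | 2 | 1.07 | 1.59 | 13% |
| 10 points | 4 | 1.14 | 1.66 | 20% |
| 20 points | 2 | 1.15 | 1.71 | 24% |
| 20 points | 4 | 1.29 | 1.89 | 36% |
| 30 points | 2 | 1.23 | 1.83 | 33% |
| 30 points | 4 | 1.47 | 2.15 | 47% |

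With OR_D = 1.0 and any gap above zero, the adjusted OR is 1.00 and the whole gender association is removed. With no gap, nothing is lost; the small negative figures reflect only the non-collapsibility of the odds ratio.

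**The case against.** A reader might infer that these three variables are established pathways from gender to care, and that the planned model would report a real disparity as none. The documents support neither. They report no gender difference in housing, knowledge or willingness, and full removal needs gender to act only through the adjusted variables. If paths run in opposite directions, adjustment could even enlarge the association.

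Nor does it help to argue that the three cannot be confounders because they do not precede or cause gender. Age, race and ethnicity do not cause gender either, and that rule would exclude them too. Selection into an HCV-positive ED sample could also link gender to these variables without any causal effect. The sound objection is narrower: the three may be consequences of gender.

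The other side can add that a gender difference net of housing, knowledge and willingness is a legitimate question, and that the plan speaks openly of an adjusted association. That stands as a reason to keep the conditional model, but not to make it the only one stated in an analysis of disparities. Reporting outcomes by arm within gender subgroups might also leave the crude gender difference visible, but the article does not promise that contrast.

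Finally, the article condenses a full protocol that is not shown, and its covariate list is open-ended. The absence of further models is therefore not held against it. What remains is what the article does state: three possible mediators are named and assigned the role of confounders.

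**Conclusion.** The point holds as a minor one. The stated model estimates at most the part of the gender difference that does not pass through housing, HCV knowledge and willingness, while its purpose is to evaluate disparities. If gender affects these variables, part of the disparity may be removed: 13% to 47% of the log odds ratio over the assumed range with a direct odds ratio of 1.5. It is removed in full only if gender acts entirely through them. If gender does not affect them, essentially nothing is lost. The documents do not show which case applies, so neither the size nor the direction of the distortion in this trial can be stated.

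The analysis is secondary and observational. The randomized comparison, the primary outcome and the interim thresholds are not touched.

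**What to change.** 1. Name as the disparity estimate the gender association adjusted for age, race and ethnicity, with study arm added.
2. Fit a second model that adds housing status, HCV knowledge and willingness to engage in care. Label it explanatory, a conditional association, and report it beside the first.
3. Stop calling these three variables confounders.

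Fixing in advance which model is the disparity estimate also prevents a choice between them after the results are seen, which the open-ended covariate list now allows. The cost is one extra model, on data the planned model already needs, and a change of wording.

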### Trial and data monitoring

In accordance with the National Institutes of Health (NIH) and the primary funding agency, the National Institute on Drug Abuse (NIDA), we have developed a Data and Safety Monitoring (DSM) plan, and the principal investigators and core, Denver-based, research team will maintain appropriate oversight and monitoring of the trial’s conduct in its entirety. As this trial is not a phase 3 trial and it was determined to be minimal risk to participants, no Data Safety Monitoring Board (DSMB) was required for this trial. The DSM plan was approved by the Colorado Multiple Institutional Review Board (COMIRB) and NIDA prior to initiating enrollment.

The core Linkage team, consisting of one of the study principal investigators, the Linkage-to-Care Trial project coordinator, and the linkage navigators, will meet quarterly to review cases, ensure fidelity to the linkage protocols, and troubleshoot challenging linkage situations. Data monitoring will be performed from the inception of participant enrollment through follow-up as captured in REDCap. The data manager will organize all data to understand total screening and enrollment, inclusion and exclusion criteria, consent, and study procedures associated with the interventions. Weekly study team meetings will occur to review screening and enrollment. Outcomes will be collected after each interim sample has been enrolled in an effort to complete interim analyses, performed by the study’s biostatistician.

### Special considerations during the COVID-19 pandemic

This trial has enrolled participants during the COVID-19 pandemic with enrollment suspended from March 13, 2020, through August 24, 2020, and from December 2, 2020, through January 29, 2021. Furthermore, during the COVID-19 pandemic, linkage-to-care and some healthcare visits transitioned to remote participant interactions. In an effort to incorporate the effect of delayed linkage-to-care and treatment initiation during the COVID-19 pandemic, we extended the time frame for which longitudinal outcomes will be collected from 12 months to up to 18 months, also modifying treatment initiation to within 18 months of enrollment.

### Research ethics approval, consent, and confidentiality

COMIRB serves as the institutional review board (IRB) of record and approved this trial on December 17, 2017. Participants will be enrolled in this trial after obtaining verbal consent. We requested, and have obtained, a waiver of documentation of written consent based on 45 CFR 46.117. We obtained a waiver of HIPAA authorization for participants in this study. Data collected as part of this project poses no more than a minimal risk of harm to privacy.

### Potential harms

Given the comparative effectiveness nature of this trial and that all research components will be fully integrated into standard care, the primary risks to patients included in this trial will be breach of confidentiality as all study procedures will be performed as routine medical care in the ED and as follow-up for those enrolled.

### Protocol amendments

Through May 16, 2022, 15 protocol amendments have occurred. See Protocol in the Additional file 1 for details.

### Access to data and dissemination policy

The primary results of this trial will be reported in accordance with CONSORT guidelines and published in a peer-reviewed journal.

## Discussion

When complete, the DETECT Hep C Linkage trial will represent the only randomized clinical trial to compare the effectiveness of different approaches to HCV linkage to care from the ED and to attempt to quantify the added benefit of a linkage navigator. Additionally, this trial will provide data on HCV linkage to care for patients identified with untreated HCV in an ED setting, a unique and promising venue for engaging patients with HCV. If linkage navigation plus clinician referral yields at least a 20% increase in HCV treatment initiation, this finding will have significant implications for clinical settings where HCV rates are high and where the addition of an HCV linkage navigator to hospital staff could yield major benefits to the community by decreasing HCV prevalence.

Rationale for the head-to-head comparison performed in this trial resulted from prior findings that clinician referral from ED settings, while current standard of care has limited effectiveness [9–11]. The benefits of a linkage navigator for HIV care after HIV diagnosis suggest that extension of linkage-to-care approaches for HCV are needed to facilitate treatment and, in turn, limit transmission [13, 24]. Until now, no prospective comparative evaluation of clinician referral to linkage navigation for HCV has been performed, particularly in an ED environment, and the findings will have important implications for clinical practice.

Potential limitations of this trial include its performance at a single academic medical center with experience performing infectious diseases screening in the ED and with integrated linkage-to-care services for HIV, but not HCV. While the navigation standard work was developed using an interdisciplinary group of programmatic and content experts and based on prior processes related to HIV screening and other navigation programs, success of navigation may be limited by complexities of navigating care for patients who are socially and economically vulnerable. Furthermore, secular trends related to the diagnosis and treatment of HCV may influence the numbers of patients identified with active chronic HCV, which may limit the ability to enroll, and conducting this trial during the COVID-19 pandemic has led to unanticipated delays and disruptions, including varying trends in access to care and the broader use of telehealth, which may also affect results. Finally, although the hypothesized effect was influenced by existing knowledge and content expertise, very little prior data existed to inform the hypothesized effect; therefore, depending on the true effect, this study may be underpowered.

## Trial status

Enrollment for this trial was initiated on November 20, 2019, with enrollment stoppage due to institutional policies related to the COVID-19 pandemic from March 13, 2020, through August 24, 2020, then again on December 2, 2020, through January 29, 2021, at which point enrollment resumed. The interim analysis occurred on August 1, 2022, without meeting a stopping rule. Complete enrollment is anticipated to finish in 2023.

## Data Availability

The investigators will have access to the final trial dataset, and the principal investigators, Drs. [name] and [name], take responsibility for the trial as a whole.
